
Interventional studies targeted to the effect of vitamin D supplementation on major cardiovascular events and using death as a primary endpoint do not yet exist. In a secondary analysis of the RECORD trial on four pre-specified outcomes, vitamin D supplementation was found to protect against cardiac failure (HR =0.75; CI 0.58 to 0.97), but not against myocardial infarction or stroke [77]. However, several recently published meta-analyses of interventional studies (whose primary endpoint was not cardiovascular events) found no (positive or negative) effect of vitamin D supplementation on major cardiovascular events [77–79], although a slight, but significant decrease in all-cause mortality was reported [79–81]. To date, the few, weakly powered, observational studies performed in RTRs have found no robust association between serum 25OHD levels and cardiovascular risk factors [35, 82, 83]. The apparent discrepancy between the strong association of vitamin D deficiency with major cardiovascular events and the lack of strong evidence of a reduction in cardiovascular risk with vitamin D supplementation may be due to reverse causation, which frequently affects observational studies (low vitamin D being the consequence rather than the cause of the disease under study).

However, because vitamin D intoxication in humans may lead to vascular calcifications, the benefit/risk ratio of supraphysiologic dosages of vitamin D should be evaluated, especially in RTRs having an increased cardiovascular risk. Indeed, a biphasic effect of vitamin D on the risk of vascular calcifications is likely [84]. It has been recently reported from observational studies that the risk of all-cause mortality [85] and the risk of major cardiovascular events [86, 87] increased if serum 25OHD levels were below 20 ng/ml but also if levels were above 40 ng/ml. Although no causality can be concluded from observational studies, these results should incline the medical community to be cautious with regard to high-dose vitamin D supplementation and cardiovascular health.

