## Methods

### Objectives

The VITALE study is designed to evaluate whether high doses of cholecalciferol in RTRs with vitamin D insufficiency has beneficial effects upon the late post-transplant outcome compared with low-dose supplementation. As a primary outcome, we will evaluate the impact of cholecalciferol on a composite endpoint including *de novo* DM (fasting glycaemia >7 mmol/l or glycaemia >11 mmol/l), major cardiovascular events (acute coronary heart disease, acute heart failure, lower-extremity arterial disease, cerebrovascular disease), *de novo* cancer, and patient death. Secondary objectives will compare the effects of high-dose versus low-dose cholecalciferol on BP and on BP control (number and dosage of antihypertensive drugs), echocardiography findings, infections (including cytomegalovirus, *Pneumocystis*, nocardial infection, cryptococcal infection, aspergillosis), acute rejection episodes, renal allograft function including Modification of the Diet in Renal Disease (MDRD)-v4 estimated glomerular filtration rate (eGFR) [88], proteinuria and graft survival, and mineral metabolism biologically (serum calcium, phosphate, 25OHD and PTH) and clinically (graft nephrolithiasis, bone mineral density, measured body weight, and incidence of fractures) relevant parameters.

We have noted that, according to the published literature, some vitamin D experts especially involved in the cardiovascular field consider that optimal 25OHD concentration for cardiovascular health probably lies within a narrow range of 30 to 40 ng/ml [89, 90]. We took this advice into account, and one of the main objectives of our VITALE trial is thus to evaluate whether our treatment scheme, which probably will increase the 25OHD concentration above 40 ng/ml in a significant percentage of patients, is safe, especially in terms of cardiovascular health.

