### Study population and sample size

The study sample will consist of 640 RTRs found to be lacking sufficient vitamin D (25OHD <30 ng/ml) 12 to 48 months post-transplantation with 320 subjects in each study group. Inclusion and exclusion criteria are detailed in the Appendix. The sample size calculation was performed according to the following assumptions: The principal criteria will be the occurrence of one of the events of the composite endpoint including *de novo* DM, major cardiovascular events, *de novo* cancer, and patient death. Over a 2-year follow-up period, we estimate, according to previous reports in the literature, that the incidence of a first event of the composite endpoint will be around 22% in our population (6% for *de novo* T2DM [91, 92], 6% for major cardiovascular events [93–95], 7% for *de novo* cancers [15, 96], and 3% for patient death). This 22% global estimated incidence does not take into account the fact that some patients may experience several events of the composite endpoint during the follow-up period. According to the results of the numerous observational studies showing an inverse association between 25OHD concentrations and various clinical events and to the results of the few interventional trials showing effects of high-dose vitamin D supplementation on these events (detailed above),we estimate that the overall decrease in the incidence risk of a first event of the composite endpoint will be around 40% in the high-dose group compared with the low-dose group (33% decrease for *de novo* DM, 40% decrease for major cardiovascular events and 50% decrease for *de novo* cancer). Thus, to demonstrate the reduction in the incidence of a first event of the composite endpoint from 22% in the low-dose group to 13% in the high-dose group, with a 90% power and 5% α risk error, 582 RTRs (291 in each group) will be required. Taking into account that 10% of patients will not be evaluable, a total of 640 RTRs will be required. The inclusion of a total of 480 RTRs would allow us to test the same hypothesis with a power of 80%.

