### Randomization and blinding

If all inclusion and none of the exclusion criteria are met and informed consent has been obtained, each RTR will be included in the study and allocated a randomization number used for assignment to one of the two treatment arms. The randomization list will be computer-generated and created using nQuery Advisor software (v6.01). The randomization will be stratified by centres, and blocks of four will be used in order to facilitate treatment distribution by the central pharmacy. The size of the blocks will be unknown to the investigators. The two treatment regimens will be randomly allocated in a 1:1 ratio. The attribution arm will be given centrally by Cleanweb® software after the validation of inclusion criteria, and this software also allows entering trial data for each patient. Participants, investigators, and outcome assessors will be blinded to the allocated treatment. Blinding will be ensured by the use of investigational products that are identical in packaging, labelling, appearance, smell, and taste. Unblinding will occur only in cases of emergency or at the conclusion of the study. In most cases, discontinuation of the treatment should be sufficient without the need for unblinding. Access to the randomization list will be restricted to the pharmacist involved in the study and a research assistant.

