All events occurring during the 2 years of follow-up will be recorded. The principal criteria (occurrence of the first event constituting the composite endpoint) will be compared between the two groups using the Cox model that takes into account the stratification by the centre. Secondary criteria will be compared using tests corresponding to the nature of the variable: *χ*^2^ or Fisher’s exact test for qualitative variables, parametric or non-parametric variance analysis for quantitative variables, and log-rank or Gray’s test for time to event. The secondary parameters that will be analysed are the following: the incidence of each of the events constituting the composite primary endpoint; BP measurement, and number, drug classes and doses of antihypertensive drugs necessary to reach normal BP; preventive coronary revascularisation; evolution of the left ventricular ejection fractions and of the left ventricular wall thickness assessed by transthoracic echocardiography; vitamin D insufficiency correction; evolution of the fasting urinary calcium/creatinine ratio and of serum calcium, phosphate, and PTH concentrations; bone fracture incidence; changes in body height; changes in bone mineral density at the lumbar spine and femoral neck; incidence of infectious episodes and type of infection; incidence of treated acute rejection episodes; evolution of MDRD eGFR, of urinary protein/creatinine ratio, and of urinary microalbuminuria/creatinine ratio; graft survival; evolution of HbA1C in the absence of DM; evolution of HbA1C and of anti-diabetic treatments in cases of *de novo* DM; or incidence of cholecalciferol-related side effects (hypercalcaemia, calcic nephrolithiasis and other spontaneously reported side effects). Adjustment for multiple testing will be performed using the Hochberg procedure for the components of the primary criteria. We will also describe in detail each adverse event (AE) that occurs during the study, and we will report the overall rate of occurrence of AE, the rate of withdrawal from the study due to an AE, the overall rate of patients with at least one clinically significant laboratory abnormality, the rate of AEs attributable to treatment (possible or probable relationship), and the rate of serious AEs. The percentage of patients with each of the AEs associated with cholecalciferol and the intensity of these AEs will be specified.

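### Cardiovascular safety is a stated main objective, but major CV events are formally compared only within the composite and under a Hochberg rule that makes no exception for harm

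*Protocol article*

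**What the plan says.** The Objectives section states that "one of the main objectives of our VITALE trial is thus to evaluate whether our treatment scheme", which is expected to take many patients above 40 ng/ml of 25OHD, "is safe, especially in terms of cardiovascular health". The Background section on the cardiovascular system gives the reason. It cites observational reports of more major CV events both at low levels and above 40 ng/ml, and says that "these results should incline the medical community to be cautious with regard to high-dose vitamin D supplementation and cardiovascular health".

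Under Study population and sample size, major CV events appear as a benefit component: 6% over 2 years in the low-dose group, with an assumed 40% fall under high dose. No harm size or safety margin is given.

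Under Statistical analysis, the composite is compared by a Cox model stratified by centre. The incidence of each component is a secondary parameter, and "Adjustment for multiple testing will be performed using the Hochberg procedure for the components of the primary criteria". No exception is made for an effect in the harmful direction.

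Other relevant information is planned. The Statistical analysis section lists blood pressure, preventive coronary revascularisation, ejection fraction and wall thickness, and adverse and serious adverse event rates. Table 1 marks echocardiography as safety data, with valvular calcifications to be notified. The Discussion acknowledges that composites can mislead when effects differ between components and promises to present every component.

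**The concern.** The testing rule works against the stated objective. Adjusting across components guards against false claims of benefit. Applied to a harm question, it makes a real excess less likely to be flagged. The composite does not fill the gap, because an increase in CV events can be absorbed by decreases in diabetes and cancer.

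This is not a detail left to an analysis plan. The article states a multiplicity rule, and that rule covers the very events named in the safety objective. What is at stake is whether the trial's answer to its own cardiovascular question rests on an analysis suited to that question.

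**Working it through.** **Inputs from the documents.** Low-dose 2-year rates: diabetes 6%, major CV events 6%, cancer 7%, death 3%. Assumed effects: diabetes −33%, cancer −50%, none on death. Allocation is 1:1, with 291 evaluable patients per arm.

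**Assumption.** The documents give no CV harm size. I use CV rates of 9% (relative risk 1.5) and 12% (relative risk 2.0) in the high-dose arm.

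**Step 1, the plan's own figure.** The stated design is a fall "from 22% in the low-dose group to 13% in the high-dose group". For this the article gives 291 patients per arm, 582 in all, at 90% power and a 5% alpha. With HR = ln(0.87)/ln(0.78) = 0.560, the Schoenfeld formula at one-sided 5% gives 103 events. Dividing by the mean event rate of 0.175 gives 589 patients, close to 582. At two-sided 5% it gives 126 events and 720 patients. So 582 is reached approximately only with a one-sided 5% test, and the article does not state the sidedness. If the primary test is one-sided for benefit, it does not test harm at all. The harm calculations below are two-sided. The total of 640 is 582 × 1.1, for the assumption that "10% of patients will not be evaluable".

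**Step 2, can the composite hide a CV increase?** Adding the component rates, as the plan does:
- CV at 9%: 0.06×0.67 + 0.09 + 0.07×0.50 + 0.03 = 0.0402 + 0.09 + 0.035 + 0.03 = 19.5%, against 22%.
- CV at 12%: 0.0402 + 0.12 + 0.035 + 0.03 = 22.5%, against 22%.
- Break-even: 0.22 − 0.0402 − 0.035 − 0.03 = 0.115, a relative risk of 0.115/0.06 ≈ 1.9.

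If the assumed benefits hold, CV events can nearly double before the composite turns unfavourable. With 19.5% v 22%, two-sided power to show a composite benefit is only about 11%. The usual result would be a null composite, not a false success.

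**Step 3, power to detect CV harm.** Power = Φ{[(p2 − p1)√n − z·√(2p̄(1 − p̄))] / √(p1(1 − p1) + p2(1 − p2))}, with p1 = 0.06 and n = 291. z is 1.960 at two-sided 0.05 and 2.498 at 0.05/4 = 0.0125, the Hochberg step that applies when no other component supports rejection.

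For p2 = 0.09: p̄ = 0.075, null term 0.3725, alternative term 0.3719, and 0.03×√291 = 0.512.
- At 0.05: (0.512 − 0.730)/0.3719 = −0.59, power 28%.
- At 0.0125: (0.512 − 0.930)/0.3719 = −1.13, power 13%.

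For p2 = 0.12: p̄ = 0.09, null term 0.4047, alternative term 0.4025, and 0.06×√291 = 1.024.
- At 0.05: (1.024 − 0.793)/0.4025 = 0.57, power 72%.
- At 0.0125: (1.024 − 1.011)/0.4025 = 0.03, power 51%.

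With 320 per arm the pairs are 30% v 14% and 76% v 56%. A simulation of the full four-component Hochberg procedure (200,000 runs, independent components, 291 per arm) agrees: 28% falls to 13–14%, and 73% falls to 52–54%.

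**Step 4, what a null CV result could show.** With 6% in both arms, events = 582 × 0.06 ≈ 35. The interval for the hazard ratio is exp(±1.96 × √(4/34.92)) = 0.52 to 1.94. On the relative-risk scale, SE = √(2×0.94/(291×0.06)) = 0.328, giving 0.53 to 1.90. Either way it is roughly 0.5 to 1.9.

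**The case against.** The strongest reply has four parts.

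**Cardiovascular safety is looked at elsewhere.** This stands. Blood pressure, revascularisation, ejection fraction, wall thickness, valvular calcification and serious adverse event rates are all planned outside the Hochberg family, and every component will be shown. A rise from 6% to 9% would be visible in the report. It would therefore be wrong to infer that CV safety is judged only through the composite and the adjusted test. What remains is narrower: none of these other items is an inferential comparison of major CV events for harm.

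**Masking and the largest power loss do not coincide.** This also stands. At a relative risk of 1.5 the composite leans favourable but would usually be null. At 2.0 the composite is 22.5%, so there is no apparent benefit to mislead anyone. The 19.5% v 22% comparison shows offsetting and does not predict a positive trial.

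**Few events limit the trial more than Hochberg does.** True. Unadjusted power for 6% v 9% is about 28%, and 80% power would need about 1,209 per arm. Removing the adjustment does not make the trial powered for such harm. This is a reason to judge safety from an interval rather than from a test.

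**The article never says that a non-significant CV test will be read as safe.** Correct. A reader might infer that the trial is set to declare safety on that basis, but the documents state no such rule. They also do not forbid an unadjusted interval, and an unseen analysis plan may provide one. The mismatch between the stated objective and the stated multiplicity rule remains.

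**Conclusion.** The point holds in a limited form. A main objective concerns cardiovascular harm, and the stated rule for testing major CV events reduces the chance of detecting it. At the strictest Hochberg step the loss is about 15 percentage points of power for 6% v 9% (28% to 13%) and about 20 for 6% v 12% (72% to 51%). These figures rest on the plan's 6% control rate, 291 evaluable patients per arm, two-sided testing and harm sizes that I assumed. The offsetting in the composite further assumes that the planned falls in diabetes and cancer occur in full.

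With or without the adjustment, about 35 CV events at a hazard ratio of 1 leave an upper limit near 1.9. A non-significant result could not establish safety. The composite comparison itself is not invalidated by this point. It is a cheap improvement.

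**What to change.** In the Statistical analysis section:
- Restrict the Hochberg procedure to claims of benefit on the components.
- Name major CV events as the key safety comparison. Report the hazard ratio from the same centre-stratified Cox model with an unadjusted two-sided 95% confidence interval, beside the composite result.
- Say that the safety statement will rest on that interval, in particular its upper limit, and not on a non-significant test.

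**Cost.** The change is to wording and reporting only, with no extra patients or data and no change to the primary analysis. The downside is one unadjusted harm comparison, with a 2.5% chance of a false harm signal, and a more guarded conclusion about safety.

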### Study population and sample size

The study sample will consist of 640 RTRs found to be lacking sufficient vitamin D (25OHD <30 ng/ml) 12 to 48 months post-transplantation with 320 subjects in each study group. Inclusion and exclusion criteria are detailed in the Appendix. The sample size calculation was performed according to the following assumptions: The principal criteria will be the occurrence of one of the events of the composite endpoint including *de novo* DM, major cardiovascular events, *de novo* cancer, and patient death. Over a 2-year follow-up period, we estimate, according to previous reports in the literature, that the incidence of a first event of the composite endpoint will be around 22% in our population (6% for *de novo* T2DM [91, 92], 6% for major cardiovascular events [93–95], 7% for *de novo* cancers [15, 96], and 3% for patient death). This 22% global estimated incidence does not take into account the fact that some patients may experience several events of the composite endpoint during the follow-up period. According to the results of the numerous observational studies showing an inverse association between 25OHD concentrations and various clinical events and to the results of the few interventional trials showing effects of high-dose vitamin D supplementation on these events (detailed above),we estimate that the overall decrease in the incidence risk of a first event of the composite endpoint will be around 40% in the high-dose group compared with the low-dose group (33% decrease for *de novo* DM, 40% decrease for major cardiovascular events and 50% decrease for *de novo* cancer). Thus, to demonstrate the reduction in the incidence of a first event of the composite endpoint from 22% in the low-dose group to 13% in the high-dose group, with a 90% power and 5% α risk error, 582 RTRs (291 in each group) will be required. Taking into account that 10% of patients will not be evaluable, a total of 640 RTRs will be required. The inclusion of a total of 480 RTRs would allow us to test the same hypothesis with a power of 80%.

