For our study, we have chosen a composite criterion for efficacy. The main advantages supporting this choice are that it increases statistical efficiency because of a higher event rate, which reduces sample size requirement. In addition, it helps investigators avoid an arbitrary choice between several important outcomes that refer to the same disease process. Composite outcomes can be misleading when treatment effects vary across components with very different clinical importance. In our study, the rate of each event except for death is of similar magnitude. Moreover, we hypothesize that the rate reduction of each event composing the endpoint will be between 30% and 50%, giving a mean reduction of 40% overall. We also hypothesize that the drug will not affect death, but death is being included in the composite endpoint because it is a competing risk with major cardiovascular events. In order to limit misleading interpretation, we will clearly present data for all components and discuss the role of each in the total reduction of the composite event rate.

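### The planned 13% high-dose event rate does not follow from the protocol's own component effects: with death unaffected they give 14.1%, and the stated 90% power becomes about 81%

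*Protocol article*

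**What the plan says.** The section Study population and sample size states that "the incidence of a first event of the composite endpoint will be around 22% in our population". The figure is the plain sum of four components: 6% for diabetes, 6% for major cardiovascular events, and "7% for *de novo* cancers [15, 96], and 3% for patient death". The section adds that this sum makes no allowance for patients who have more than one event.

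The assumed effects are given in the same section as "33% decrease for *de novo* DM, 40% decrease for major cardiovascular events and 50% decrease for *de novo* cancer". No effect on death is listed. From these the protocol takes an overall reduction of around 40% and sizes the trial for a fall "from 22% in the low-dose group to 13% in the high-dose group, with a 90% power and 5% α risk error". This gives 582 evaluable patients, raised to 640 for 10% non-evaluable. A fallback of 480 included patients is said to give 80% power.

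The Discussion, under Risk analysis, returns to the effect size. It puts the component reductions between 30% and 50%, "giving a mean reduction of 40% overall", and then says: "We also hypothesize that the drug will not affect death".

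**The concern.** A composite made of four added components can only fall by the weighted effect on all four. If one component (death, 3 of the 22 points) is assumed not to change, the overall reduction must be smaller than the reduction in the other three. The protocol uses about the same figure for both.

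The difference between 22% and 13% underlies both power statements. If the stated hypotheses produce a smaller effect, the trial has less power against its own hypothesis than the protocol says. A null result would then be read against 90% power that the stated assumptions do not deliver.

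**Working it through.** **Inputs.** Component rates and reductions, 582 evaluable patients (291 per group), 480 included, 10% non-evaluable and 5% alpha come from Study population and sample size. No effect on death comes from Risk analysis. The primary analysis is a Cox model for time to first event (Statistical analysis), so a log-rank power formula is appropriate. The protocol does not say whether the 5% is one- or two-sided.

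**Formulas.** HR = ln(1 − p₂)/ln(1 − p₁). Expected events D = n per group × (p₁ + p₂). Events required = 4(z_α + z_power)²/(ln HR)². Power = Φ(½√D·|ln HR| − z_α), with z_α = 1.645 one-sided or 1.960 two-sided.

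**Step 1: reproduce the protocol's figures.** For 22% versus 13%, HR = ln 0.87/ln 0.78 = 0.5605 and |ln HR| = 0.579.
- 90% power, one-sided 5%: 4(1.645 + 1.282)²/0.579² gives 103 events. Dividing by the mean event rate of 0.175 gives 589 patients, against 582 stated.
- 80% power, one-sided 5%: 74 events, 423 evaluable, and 423/0.9 = 470 included, against 480 stated.
- 582 × 1.10 = 640.
- The two-sided methods tried need 720 to 790 patients for 90% power, so they do not reproduce 582.

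The stated figures therefore correspond closely to a one-sided 5% log-rank calculation, with 480 counted before the 10% loss.

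**Step 2: high-dose rate from the stated components.**
6 × 0.67 + 6 × 0.60 + 7 × 0.50 + 3 × 1.00 = 4.02 + 3.60 + 3.50 + 3.00 = 14.12%.
- Reduction: 1 − 14.12/22 = 35.8%. The planned 22% to 13% is 1 − 13/22 = 40.9%.
- HR = ln 0.8588/ln 0.78 = 0.613.

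**Step 3: what the 40% corresponds to.** The simple mean of 33, 40 and 50 is 41%. The weighted reduction over the 19 non-fatal points is 1 − 11.12/19 = 41.5%. Both leave death out. To reach 13%, death would have to be 13 − 11.12 = 1.88%, a reduction of 1 − 1.88/3 = 37%.

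**Step 4: power, control rate held at 22%.**

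| Evaluable patients | Test (5%) | At 13% | At 14.12% |
|---|---|---|---|
| 582 | one-sided log-rank | 89.9% | 80.7% |
| 432 (480 included) | one-sided log-rank | 80.8% | 69.8% |
| 480 (no loss) | one-sided log-rank | 84.3% | 73.8% |
| 582 | two-sided log-rank | 83.2% | 70.9% |
| 582 | two-sided, pooled proportions | 81.7% | 69.6% |

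Example, first row: at 13%, D = 291 × 0.35 = 101.85, and ½ × 10.09 × 0.579 − 1.645 = 1.276, so Φ = 0.899. At 14.12%, D = 291 × 0.3612 = 105.1 and |ln HR| = 0.490, and ½ × 10.25 × 0.490 − 1.645 = 0.867, so Φ = 0.807.

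**Step 5: sensitivity to overlap.** The documents give no overlap figure. As an assumption, let a share f of deaths follow another component event, so that they are not first events. One-sided log-rank, 582 patients:

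| f | Low vs high dose | Reduction | Power |
|---|---|---|---|
| 0 | 22.0% vs 14.1% | 36% | 81% |
| 0.5 | 20.5% vs 12.6% | 38% | 83% |
| 1 | 19.0% vs 11.1% | 41.5% | 86% |

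If instead all four components overlap independently, the rates are 20.3% versus 13.4%, a 34% reduction.

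**The case against.** The strongest counter-argument is overlap. The endpoint is the first event, and the protocol itself warns that the 22% ignores multiple events. A death after a diabetes, cardiovascular or cancer event does not count again, so the unaffected 3% may be diluted and an overall reduction near 40% becomes possible. This stands in part: 14.1% is the additive reading, not the only possible value. But the additive reading is the protocol's own, since that is how it reaches 22%. Overlap also lowers the control rate. Even if every death follows another component event, one-sided power is only about 86%.

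A second argument is rounding, since the protocol says around 40%. An exact 40% gives 13.2% and 88.5% power, so rounding explains about 1.4 of the 9 points.

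Three stronger readings are tempting but not supported.
- A reader might infer that Risk analysis flatly contradicts itself, because it says each event falls by 30–50% and then that death does not fall. The text sets death apart just before and just after, so this is better read as loose wording about the three non-fatal components. What is wrong there is the overall 40%.
- A reader might set the two-sided power with all 480 analysed (61–63%) against the stated 80%. That mixes this error with the separate question of sidedness. The stated 80% reproduces one-sided with about 432 evaluable, and the like-for-like fall is from 81% to 70%.
- A reader might conclude that a power for 640 patients is also wrong. The protocol gives none; 640 is 582 raised for non-evaluable patients.

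**Conclusion.** The point holds. The 13% is inconsistent with the component effects and the no-effect-on-death hypothesis that the protocol states; together these give 14.1%, a 36% reduction. On the basis that reproduces the protocol, the cost is about 9 points of power with 582 evaluable patients and about 11 points with 480 included.

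The size rests on three assumptions: a control rate of 22%, additive components, and one-sided 5% alpha. With a two-sided test the loss due to this error is about 12 points with 582 patients. The further gap between 82–83% and the stated 90% then belongs to the unstated sidedness, not to this error. With some overlap between deaths and other events the shortfall is smaller, but none of the overlap cases examined reaches 90%. The error does not affect the endpoint, the analysis or the conduct of the trial.

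**What to change.** In Study population and sample size, keep 22% versus 13% on record as the basis on which the 582 and 640 were set. Add that the stated component effects with death unaffected imply about 14.1%, a 36% reduction. Restate the power for 582 evaluable and 480 included patients at that effect, under one declared alpha convention (one- or two-sided). One-sided, this is about 81% and about 70%. If 13% is to stand as the hypothesis, state and justify a mortality reduction of about 37% and withdraw the statement that death is unaffected.

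In Risk analysis, say that the 30–50% reductions apply to the three non-fatal components, with none for death, giving about 36% overall.

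The cost is rewording in two places and a less favourable power statement. No extra patients are needed for this correction, and nothing changes in the endpoint, the analysis or the ongoing recruitment.

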**Discussion:**

We previously reported that the intensive cholecalciferol treatment (100 000 IU every 2 weeks for 2 months) was safe in RTR. Using a pharmacokinetic approach, we showed that cholecalciferol 100,000 IU monthly should maintain serum 25-hydroxyvitamin D at above 30 ng/ml but below 80 ng/ml after renal transplantation. Taken together, these results are reassuring regarding the safety of the cholecalciferol doses that will be used in the VITALE study. Analysis of data collected during the VITALE study will demonstrate whether high or low-dose cholecalciferol is beneficial in RTRs with vitamin D insufficiency.

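### The sample sizes of 582 and 480 do not give 90% and 80% power for 22% versus 13% at two-sided 5%; the rates, the sidedness and the sizes need to be reconciled

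*Protocol article*

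**What the plan says.** The section on study population and sample size gives all the inputs. The two-year incidence of a first event is to fall "from 22% in the low-dose group to 13% in the high-dose group". The basis is that "the overall decrease in the incidence risk of a first event of the composite endpoint will be around 40" per cent. It then states: "with a 90% power and 5% α risk error, 582 RTRs (291 in each group) will be required". On losses: "Taking into account that 10% of patients will not be evaluable, a total of 640 RTRs will be required". It adds: "The inclusion of a total of 480 RTRs would allow us to test the same hypothesis with a power of 80" per cent.

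Neither that section nor the statistical analysis section says whether the 5% is one-sided or two-sided. Two other places bear on the question. The Discussion paragraph of the abstract says that the data "will demonstrate whether high or low-dose cholecalciferol is beneficial in RTRs with vitamin D insufficiency". The Objectives section says, about safety and cardiovascular safety in particular, that "one of the main objectives of our VITALE trial is thus to evaluate whether our treatment scheme" is safe. Allocation is equal: "The two treatment regimens will be randomly allocated in a 1:1 ratio". The primary comparison is a Cox model for the first event that takes account of stratification by centre.

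**The concern.** A sample size statement should be recoverable from its own inputs. Here the rates, alpha, power and group size are all printed, and at a two-sided 5% level they disagree by far more than a choice of formula can explain. Readers normally take an unqualified 5% alpha as two-sided, and the aims quoted above allow for a result in either direction.

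At stake is the stated chance of detecting the planned effect. If the rates are as printed and the test is two-sided, the risk of missing a true fall from 22% to 13% is about 17 to 19% with 582 evaluable patients, not 10%. With 480 patients it is about 24 to 31%, not 20%. A null result would then be read with more confidence than the design supports. If a rate is misprinted instead, the trial is powered for a larger effect than the one that the article justifies.

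**Working it through.** **Inputs**, all from the sample size section unless noted: p1 = 0.22, p2 = 0.13; alpha 5%, sidedness not stated; power 90% at 291 per group and 80% at 480 in total; 10% not evaluable; 1:1 allocation (randomization section).

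Derived values: difference 0.09; mean rate 0.175; p1q1 + p2q2 = 0.1716 + 0.1131 = 0.2847. Assuming proportional hazards, HR = ln(0.87)/ln(0.78) = 0.560.

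**Step 1. Size needed for 90% power, two-sided 5%, 22% versus 13%.**
- Two proportions, pooled: n per group = [1.960·√(2 × 0.175 × 0.825) + 1.282·√0.2847]² / 0.09² = 372.5, so 373, or 746 in total.
- Unpooled: (1.960 + 1.282)² × 0.2847 / 0.0081 = 369.3 per group.
- Schoenfeld: events = 4(1.960 + 1.282)² / (ln 0.560)² = 125.4; 125.4 / 0.175 = 717 in total.
- Freedman is slightly higher, at 378.5 per group or 757 in total.

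None is near 582.

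**Step 2. Power at the sizes in the article, 22% versus 13%.**

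| Patients analysed | Test at 5% | Pooled | Schoenfeld | Freedman |
|---|---|---|---|---|
| 582 | two-sided | 81.7% | 83.2% | 81.1% |
| 640 (all enrolled) | two-sided | 85.2% | 86.5% | 84.6% |
| 480 (all evaluable) | two-sided | 73.9% | 75.6% | 73.3% |
| 432 (480 less 10%) | two-sided | 69.3% | 71.1% | 68.8% |
| 582 | one-sided | 88.9% | 89.9% | 88.4% |
| 432 (480 less 10%) | one-sided | 79.5% | 80.8% | 78.9% |

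Example, pooled at 291 per group, two-sided: (0.09·√291 − 1.960 × 0.5374) / 0.5336 = 0.90, which gives 81.7%.

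**Step 3. Where could 582 and 480 come from?**
- *One-sided 5%, 22% versus 13%.* For 90% power: Schoenfeld 584, unpooled 602 (301 per group), pooled 608 (304 per group). For 80%: Schoenfeld 422, and 422 × 1.1 = 464; unpooled 217.3 per group, so 218, and 436 × 1.1 = 479.6. The stated power is recovered approximately. But Schoenfeld fits 582 and misses 480, while the unpooled formula fits 480 and misses 582.
- *Two-sided 5%, 22% versus 12%, unpooled.* The variance sum is 0.1716 + 0.1056 = 0.2772. For 90%: 10.507 × 0.2772 / 0.01 = 291.3 per group (stated: 291). For 80%: 7.849 × 0.2772 / 0.01 = 217.6, so 218 per group, and 436 × 1.1 = 479.6 (stated: 480). Both sizes match, with the same factor of 1.1 that turns 582 into 640 (582 × 1.1 = 640.2).

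The second route fits better, but it contradicts the printed text. A fall from 22% to 12% is 10/22 = 45%. A 40% reduction gives 22% × 0.6 = 13.2%, which agrees with the printed 13%.

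**Step 4. Losses.** With 10% not evaluable, 640 leaves 640 × 0.9 = 576, not 582; the inflation should be 582/0.9 = 647. The effect is small: two-sided pooled power is 81.3% at 576 against 81.7% at 582.

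**The case against.** A reader might infer that the trial was designed with a one-sided test and that this explains the numbers. The documents do not establish it. The article never says one-sided, no single one-sided formula checked reproduces both sizes, and a two-sided calculation with 12% fits both. The cause is open, and only the sponsor's own calculation can settle it.

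It can also be argued that a two-sided test is not strictly required. The sample size section speaks of showing a reduction, the conclusion says that the study was designed to show that high doses reduce risk, and harm is covered by separate adverse event reporting. A condensed article may leave sidedness to the full protocol. This stands in part: silence on sidedness alone would not be a finding. But the stated power fails under the usual reading of the alpha, and the abstract and the safety objective both favour that reading.

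A third objection is that the intention-to-treat analysis keeps all patients, so 640 rather than 582 may be the right number. That is fair, and it raises two-sided power to about 85 to 86%, which is still short of 90%. It assumes that 22% and 13% hold in all 640, although the article treats patients lost to follow-up as failures. The same argument favours the upper range, 73 to 76%, for 480.

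Finally, a reader might see 480 as a planned fallback or a ground for stopping recruitment early. The article mentions it only conditionally, attaches no rule to it, and aims for 320 per group with analysis at the end of the study.

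**Conclusion.** The point holds as an inconsistency between stated inputs and stated power. At 22% versus 13%, two-sided 5%, power is about 82% with 582 evaluable (81 to 83%), about 85 to 86% with all 640 analysed, and 69 to 76% with 480, depending on how many are evaluable. Ninety per cent needs about 717 to 746 evaluable patients by the Schoenfeld and pooled formulas.

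This rests on the printed rates, equal allocation, a two-sided test and, for the time-to-event formulas, proportional hazards. Taking an exact 40% reduction (13.2%) lowers pooled power at 582 to 79.8%.

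Either the test behind the calculation was one-sided and undeclared, or the rate used was 12% rather than 13%. Under both explanations, something in the printed statement needs correcting. The loss adjustment (576 against 582) is a minor slip and does not drive the conclusion.

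**What to change.** Retrieve the original calculation and confirm which rates, sidedness and formula were used. State that the primary Cox comparison is two-sided at 5%. Then do one of the following:

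- **If 13% was the design rate:** restate power as about 82% with 582 evaluable, about 85 to 86% if all 640 are analysed, and about 69 to 76% with 480. Remove the 80% label from 480.
- **If 12% was the design rate:** correct 13% to 12% and the reduction from about 40% to about 45%, and give the support for that larger effect. The stated 90% and 80% can then stand for that effect.

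In either case, note that 640 enrolled with 10% not evaluable leaves 576.

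The change is to wording only and needs no extra patients. Its price is a less favourable statement: either lower power or a more ambitious target effect.
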